## Abstract

**Background:**

Only 7.8 % of individuals meeting diagnostic criteria for alcohol use disorder (AUD) receive treatment in a given year. Most individuals with AUDs are identified in primary care (PC) settings and referred to substance use disorders (SUD) clinics; however, only a minority of those referred attend treatment services. Safe and effective pharmacological treatments for AUD exist, but they are rarely prescribed by PC providers. The objective of this study is to refine, implement, and evaluate an intervention to integrate pharmacological AUD treatment options into PC settings. This paper provides a detailed description of the intervention design and the evaluation components.

**Methods/design:**

Three large Veterans Health Administration (VHA) facilities are participating in the intervention. The intervention targets stakeholder groups with tailored strategies based on implementation theory and prior research identifying barriers to implementation of AUD pharmacotherapy. Local SUD providers and primary care mental health integration (PCMHI) providers are trained to serve as local implementation/clinical champions and receive external facilitation. PC providers receive access to consultation from local and national clinical champions, educational materials, and a dashboard of patients with AUD on their caseloads for case identification. Veterans with AUD diagnoses receive educational information in the mail just prior to a scheduled PC visit. Effectiveness of the intervention will be evaluated through an interrupted time series with matched controls to monitor change in facility level AUD pharmacotherapy prescribing rates. Following Stetler’s four-phase formative evaluation (FE) strategy, FE methods include (1) developmental FE (pre-implementation interviews with champions, PC providers, and Veterans), (2) implementation-focused FE (tracking attendance at facilitation meetings, academic detailing efforts by local champions, and patient dashboard utilization), (3) progress-focused FE (tracking rates of AUD pharmacotherapy prescribing and rates of referral to PCMHI and SUD specialty care), and (4) interpretive FE (post-implementation interviews with champions and PC providers). Analysis of FE data will be guided by the Consolidated Framework for Implementation Research (CFIR).

**Discussion:**

If demonstrated to be successful, this implementation strategy will provide a replicable, feasible, and relative low-cost method for integrating AUD treatment services into PC settings, thereby increasing access to AUD treatment.

## Background

The ADAPT-PC protocol provides a detailed description of an intervention to improve access to evidence-based pharmacological treatments for alcohol use disorders (AUD) in primary care settings that was designed to be easily scalable and relatively inexpensive. The protocol also provides a detailed description of how implementation frameworks and methods can be used to inform the design, refinement, and evaluation of an implementation intervention.

In 2013 in the USA, 16.6 million adults (7.0 %) met diagnostic criteria for an AUD and 6.8 % of the population engaged in heavy drinking (five or more drinks on five or more days out of the past 30 days) [1]. AUDs and heavy drinking are associated with car crashes, domestic violence, neurocognitive impairments, poor medication adherence, psychiatric comorbidity, and increased morbidity and mortality [2–8]. The total societal costs of AUDs and heavy drinking, including health care costs, law enforcement costs, other direct costs (e.g., material losses due to accidents), and productivity losses were estimated in 2006 to be over $131 billion dollars, representing 1 % of the total US Gross Domestic Product [9]. Despite the high prevalence and costs associated with AUDs, treatment rates in the general population remain astonishingly low. In 2013, only 7.8 % of individuals meeting diagnostic criteria for AUD received any AUD treatment [6]. Improving access to evidence-based treatments for AUD has the potential to realize savings in health care costs given the multiple chronic conditions that are exacerbated by AUD and the high rate of accidental injury associated with heavy drinking and AUD.

The under-treatment of and costs associated with AUD are also major problems within the Veterans Health Administration (VHA). In fiscal year 2010, 360,729 VHA patients had an AUD diagnosis but only a third of these patients received treatment in one of VHA’s 220 specialty addiction programs [10]. Yu and colleagues found that the marginal yearly treatment cost (cost above the mean for the entire sample) associated with a diagnosis of an AUD was $3124 (1999 dollars) per patient [11].

Clearly, different models are needed to increase access to treatment for the majority of individuals with AUD that are not currently receiving treatment. Although the need is great and interest in the integration of AUD treatment into primary care settings is high, few models for implementation of AUD treatment into primary care have been tested. Pharmacotherapy for AUD using naltrexone or acamprosate is a vastly underutilized evidence-based treatment for AUD that may have more potential for integration into primary care settings relative to intensive behavioral or psychosocial treatments.

Randomized controlled trials and meta-analyses support the efficacy of pharmacological treatment with naltrexone or acamprosate to improve drinking outcomes including time to relapse, drinking days, and number of drinks per drinking day [12–15]. Use of naltrexone or acamprosate for patients with AUD is supported by National Quality Forum’s National Voluntary Consensus Standards for the Treatment of Substance Use Conditions published in 2007 and the VA-Department of Defense (DoD) Clinical Practice Guidelines (CPG) for Management of Substance Use Disorders (SUD) updated in 2009.

Despite the evidence supporting the use of naltrexone and acamprosate for treating AUD, these medications are underutilized in the USA [16]. While over 11 million individuals in the USA met criteria for AUD in 2006 [6], only an estimated 674,000 prescriptions were filled for AUD medications (includes disulfiram as well as naltrexone and acamprosate) [16]. If each prescription was for a unique individual (a highly unlikely scenario), then only 6 % received pharmacotherapy.

Among the 440,000 VHA patients with a documented AUD diagnosis in fiscal year 2012, only 5.8 % received any approved AUD pharmacotherapy. There is also extreme variability in prescribing rates at the facility level. The rate of pharmacotherapy for AUD among Veterans who received AUD specialty care ranged from 0 to 20 % by facility with substantially lower prescribing rates for Veterans with no contact with AUD specialty care [17]. Extremely low prescribing rates and significant variation across facilities suggests that significant gaps exist in access to these medications and that more could be done to increase prescribing rates.

### Diagnosing the causes of quality/performance gaps

Previous work conducted by team investigators has indicated that the most predominant barriers to implementation of AUD pharmacotherapy include (1) perceived low patient demand, (2) pharmacy or formulary restrictions, (3) inadequate provider training in the use of AUD medications, (4) lack of provider confidence in the effectiveness of AUD medications, and (5) lack of patient awareness of AUD medications [18, 19]. This foundational work has led to the identification of key strategies to overcome these barriers and promote implementation of AUD pharmacotherapy including (1) educating providers about the effectiveness and appropriate use of AUD medications, (2) educating patients about AUD medication options, (3) activating patients to discuss AUD medication options with their providers, (4) increasing physician involvement in AUD treatment, (4) identifying, training, and supporting local role models or champions, and (5) facilitating connections between providers and local AUD specialists. This paper describes the development of an implementation trial to increase AUD pharmacotherapy prescribing rates in primary care.

## Methods/design

This trial will examine the feasibility, acceptability, and effectiveness of an implementation intervention to improve rates of AUD pharmacotherapy prescribing in primary care settings in three VHA facilities. The intervention includes training local clinical champions to provide education and support to primary care providers, an educational website that includes access to provider-specific dashboards for case identification, and mailing of educational materials to identified veterans. The primary outcome is prescribing rates which will be examined through an interrupted time-series analysis with matched control comparisons. Formative evaluation and a cost assessment will assess feasibility and acceptability of the intervention and inform quantitative results.

### Theoretical model

The theory of planned behavior was selected to further guide the development of our intervention components because the trial was designed to change individual behaviors: physicians’ decisions to discuss and prescribe AUD medications and patients’ decisions to discuss AUD pharmacotherapy with their provider [20]. The theory of planned behavior hypothesizes that intention to act is driven by one’s *attitude toward the behavior*, one’s *subjective perception of peer norms* related to the behavior, and one’s *perceived behavioral control* (ability to perform the behavior). Combining the recommendations from the foundational description of barriers with the theory of planned behavior, we selected the strategies described in Table 1 for inclusion in our multifaceted implementation intervention.

**Table 1 Tab1:** Multifaceted implementation intervention strategies

Local clinical champions	Primary care providers	Veterans
• 1.5-day collaborative learning session • Monthly facilitation teleconferences • On-demand access to national clinical and implementation champions • Access to website with patient and provider educational materials • Access to patient dashboard at facility level	• Educational outreach provided by local champions in large group (Grand Rounds) and small group (practice team) settings • On-demand access to national and local clinical champions • Access to website with patient and provider educational materials • Access to patient dashboard at the provider level • Reminder emails when new patients added to provider level dashboard	• Patient educational materials mailed to home address

### Selection and recruitment of sites

Three large VHA medical facilities were recruited to participate in this trial. Sites were chosen based on the availability of SUD specialty care providers and Primary Care Mental Health Integration (PCMHI) providers interested in training as local clinical champions. While participating sites were somewhat above average in overall prescribing rates of AUD pharmacotherapy for VHA medical facilities, very little of that prescribing was occurring outside of SUD specialty clinic settings where only a fraction of patients with AUD diagnoses receive treatment, indicating plenty of room for improvement in our targeted population (Veterans with AUD seen in primary care clinics).

### Phase 1: developmental formative evaluation

To understand patient perspectives on pharmacological treatments for AUD and barriers and facilitators to their use of pharmacological treatments, ten veterans with self-identified alcohol misuse will be recruited for interviews at each site. Interview questions will be guided by the theory of planned behavior to address attitudes toward AUD medications (including their perceived safety and efficacy), perceived peer norms regarding AUD medications, and perceived ability to discuss AUD medications with their provider and use the medications consistently and appropriately. Veterans will also have the opportunity to review the patient educational materials and will be queried regarding their likely response to receiving educational materials in the mail, any privacy concerns they may have with this plan, alternative methods of making the materials available, and any suggestions for additional information/materials that they would find helpful.

To understand primary care providers’ perspectives on pharmacotherapy for AUD and barriers and facilitators to prescribing pharmacotherapy for AUD in primary care settings, eight to ten primary care providers will be recruited for interviews at each site. Interview questions will be guided by the theory of planned behavior to address knowledge of and attitudes toward the use of AUD medications, perceived peer norms regarding prescribing AUD medications, and perceived ability to integrate AUD pharmacotherapy into their practice. Interview questions will also address Consolidated Framework for Implementation Research (CFIR) constructs to identify local barriers and facilitators to implementation that will need to be addressed by the intervention [21]. Providers will also have an opportunity to review the provider educational materials to provide their input as to which tools and what formats of dissemination would be most helpful. Finally, providers will have an opportunity to review the patient educational materials and will be informed of the intent to mail the materials to patients so that they can express any concerns related to this strategy or suggest modifications to the strategy.

To understand how to best assist clinical champions in their role, each site’s participating local clinical champions (SUD specialty care prescriber and PCMHI provider) will complete brief interviews to provide input into the final planning of a collaborative learning session which will serve as the starting point of the intervention. Questions will assess whether and how prescribers currently use AUD medications in their practice, what they want to learn about AUD pharmacotherapy, what formats they prefer for learning, and what they feel they would need to learn to provide support to primary care prescribers. These interviews will also include questions related to CFIR constructs for the purpose of identifying local barriers and facilitators to implementation.

Qualitative data collected during developmental interviews will be analyzed using rapid qualitative analysis techniques so that the data can be used to inform the final details of the intervention plan [22].

### Phase 2: three site feasibility trial of a multifaceted implementation intervention

#### Site champion intervention

The site champion intervention incorporates empirically based education and implementation methods including participatory and interactive education, follow-up, and performance feedback [23–28].

Two site champions from each site (a SUD specialty care prescriber and PCMHI provider) will be contacted by the Project Coordinator to complete informed consent and their pre-training interview (describe above). Once interviews are complete, we will schedule the in-person collaborative learning session. All efforts will be made to ensure that both participants from each facility are available to attend. While the session will include a didactic component, the majority of the session will be collaborative and involve group discussions. The goals of the in-person collaborative session are to ensure that all champions are knowledgeable about (1) identifying risky/heavy drinking and AUDs, (2) brief interventions for risky/heavy drinking, and (3) pharmacological and behavioral treatment options for AUDs. Additional goals are to (1) increase champions’ capability to facilitate the consideration of AUD pharmacotherapy by primary care prescribers at their site and (2) assist champions in identifying local options for providing disease care management for AUD patients receiving pharmacotherapy.

Following the in-person collaborative learning session, attendees will receive external facilitation in the form of monthly teleconference meetings for 9 months to review the agreed upon outreach plans, monitor progress, and identify implementation barriers and strategies to overcome them. Additional resources such as an email group and access to an external expert consultant upon request will also be available during that time. Finally, the site champions will receive quarterly feedback reports on the prescribing rate at their site as well as at the other participating facilities. The external facilitators will address the feedback reports and help champions interpret and apply the information learned.

#### Primary care prescriber intervention

Veterans at each site who have received a diagnosis of AUD or an Alcohol Use Disorders Identification Test—Consumption Questions (AUDIT-C) score of greater than 8 in Outpatient Patient Care Encounter files within the past 12 months, do not have an active prescription for an AUD medication (naltrexone, acamprosate, or disulfiram), and have an upcoming primary care appointment within the next 30 days will be identified on a rolling basis (once per month for 9 months) for inclusion in the cohort. Once a veteran is included, their primary care provider will be identified and the provider’s electronic contact information will be collected for the purposes of providing real-time case identification for primary care providers.

On a weekly basis during the 9-month intervention period, the project web application will automatically send email invitations to primary care prescribers at the intervention sites that have a patient in the target cohort scheduled in their clinic within the next 7 days. The email will describe the project goals and design. It will provide a link to the project website where prescribers will have access to patient and provider educational materials and contact information for the national clinical champions and the local SUD specialty care and PCMHI champions. The provider will also be able to click on a link to access the list of identified patients on their panel with appointments upcoming in the next 7 days. Following the initial email, primary care providers will receive an email alert when they have a new upcoming appointment with a patient with an AUD diagnosis.

#### Veteran intervention

Each month, veterans newly added to the cohort will be mailed educational materials. Veterans will only be mailed materials once during the intervention even if they qualify for the cohort during more than 1 month. Patients will be sent a cover letter presenting the mailing as general educational information for VHA patients including “tips” for planning a conversation about their alcohol use with their primary care provider and an educational brochure titled Medication-Assisted Treatment for Alcohol Dependence developed by the VHA Office of Informatics and Analytics as part of a toolkit to support implementation of the VA/DoD Substance Use Disorders Clinical Practice Guideline (http://www.healthquality.va.gov/guidelines/MH/sud/SUDTool3PatientBookletFinalHiRes.pdf).

### Evaluation

The evaluation includes (1) the quantitative evaluation of the impact of the intervention on the primary outcome of AUD pharmacotherapy prescribing rate, (2) a formative evaluation designed using Stetler’s four-phase formative evaluation model [29], and (3) a cost assessment.

#### Effectiveness of the implementation intervention

The primary evaluation of the intervention’s effectiveness will use an interrupted time-series design to compare post-intervention outcomes and trends to pre-intervention levels within the three intervention sites. This approach is most powerful and provides the best control for facility characteristics, because sites are compared to themselves. However, this approach is vulnerable to confusing intervention effects with secular trends or disruptions that affect all sites in the system. Therefore, we will conduct sensitivity analyses using comparison sites as controls. For each intervention site, candidate comparison sites will be identified by closely matching on several variables including SUD specialty care and non-specialty care AUD prescribing rates, overall AUD diagnosis rates, and facility size. One site will be randomly selected from the identified close matches for each intervention site. Monitoring of prescribing trends will occur exclusively through the use of available administrative data. No intervention or other activities will occur at the comparison sites.

#### Primary hypothesis 1

The rate of receipt of AUD medications among directly targeted patients will increase in magnitude after the onset of the intervention.

The primary outcome will be the proportion of veterans diagnosed with AUD on an encounter within the past 12 months who have an upcoming primary care appointment who fill a prescription for AUD medications within 1 month of the targeted appointment. This rate will be calculated monthly for a 16-month pre-intervention period and then during the 9-month intervention period. Because the optimal timeframe for observing the desired outcome is unknown, sensitivity analyses will be conducted on the follow-up duration (e.g., 2- and 3-month post-primary care visit). Using a mixed-effects, segmented logistic regression analysis, we will evaluate if there are changes in either the level or slope following the onset of the intervention.

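### The written primary outcome does not match the targeted patients of primary hypothesis 1: it does not exclude active prescriptions, does not limit fills to new starts, and omits AUDIT-C-only patients

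*Protocol article*

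**What the plan says.** The hypothesis (Protocol article, Primary hypothesis 1) reads: "The rate of receipt of AUD medications among directly targeted patients will increase in magnitude after the onset of the intervention".

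The Primary care prescriber intervention section says who is targeted. The entry route is "Veterans at each site who have received a diagnosis of AUD or an Alcohol Use Disorders Identification Test" (consumption questions) "score of greater than 8 in Outpatient Patient Care Encounter files within the past 12 months". Patients must also "do not have an active prescription for an AUD medication (naltrexone, acamprosate, or disulfiram"), and those who "have an upcoming primary care appointment within the next 30 days will be identified on a rolling basis", once a month for 9 months.

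The outcome sentence under Primary hypothesis 1 takes as its denominator and event "veterans diagnosed with AUD on an encounter within the past 12 months who have an upcoming primary care appointment who fill a prescription", with the event completed as those who "fill a prescription for AUD medications within 1 month of the targeted appointment". The rate is computed monthly for 16 months before and 9 months during the intervention. A mixed-effects segmented logistic regression then looks for a change in level or slope.

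**The concern.** The two definitions differ in three ways, and the article nowhere says that the cohort criteria carry over to the outcome.

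- **Active prescriptions.** The cohort excludes them; the outcome denominator does not.
- **Type of fill.** Because existing users are not excluded and the event is any fill, a routine refill counts as a success.
- **AUDIT-C route.** Patients who enter on AUDIT-C alone are mailed materials and trigger provider alerts, but the outcome does not count them.

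The rate that is analysed would then not be the rate that the hypothesis names. A pool of refills raises the baseline rate, which pulls the odds ratio for new starts towards 1. Patients who start because of the intervention can return in later months as refills, so a one-time step in starts looks partly like a rising trend. Level and slope are the two quantities tested. Primary hypothesis 2 and secondary hypothesis 1 are described as fully parallel to this analysis, and secondary hypothesis 1 also removes the targeted patients, so one fixed definition is needed throughout.

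**Working it through.** The article gives no sample size, power or effect size, so there is no stated figure to reproduce. The check sets the definitions side by side and then illustrates the consequence under assumed values.

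**1. Definitions**

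| Element | Targeted cohort | Primary outcome as written |
|---|---|---|
| Entry in past 12 months | AUD diagnosis or AUDIT-C > 8 | AUD diagnosis only |
| Active AUD prescription | Excluded | Not excluded |
| Appointment | Primary care, within 30 days | Upcoming primary care |
| Event | – | Any fill within 1 month |

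**2. Dilution by refills**

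Let a be the share already on medication, f the probability that such a patient refills in the month, and p the new-start rate. The measured rate is q = a·f + (1 − a)·p. All three inputs are assumptions. The 5.8% in the last two rows is the share of VHA patients with AUD who received any approved medication in fiscal year 2012 (Background). It is a system-wide annual figure, used only as an anchor.

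| a | f | p before → after | q before → after | Refill share before | True OR | Measured OR | Measured difference |
|---|---|---|---|---|---|---|---|
| 2% | 0.6 | 1% → 2% | 2.18% → 3.16% | 55% | 2.02 | 1.46 | 0.98 points (true 1.00) |
| 5% | 0.8 | 0.5% → 1% | 4.475% → 4.95% | 89% | 2.01 | 1.11 | 0.475 points (true 0.50) |
| 5.8% | 0.5 | 2% → 4% | 4.78% → 6.67% | 61% | 2.04 | 1.42 | 1.88 points (true 2.00) |
| 5.8% | 0.8 | 2% → 4% | 6.52% → 8.41% | 71% | 2.04 | 1.32 | 1.88 points (true 2.00) |

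Worked example, row 1: before = 0.02·0.6 + 0.98·0.01 = 0.0218; after = 0.012 + 0.98·0.02 = 0.0316; OR = (0.0316/0.9684)/(0.0218/0.9782) = 1.46.

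The first two rows are the extremes of the range a = 2–5%, f = 60–80%, p = 0.5–1%. The absolute difference shrinks only by the factor 1 − a, but it sits on a higher and therefore noisier base rate. In a simple two-period comparison (two-sided 0.05, 80% power), the n per period in the last two rows rises from 1,141 to 2,387 and 3,055, that is 2.1- and 2.7-fold.

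**3. Step turned into slope**

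Let new starters join the pool: a(next month) = a·(1 − d) + (1 − a)·p·v, where d is monthly discontinuation and v is the share of a month's starters carried into the pool. Take p = 2% until month 16 and 4% from month 17, with f = 0.8. With d = 0.2 and v = 0.33, the pool settles before the intervention at 0.0066/0.2066 = 3.19%.

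- Before: 0.0319·0.8 + 0.9681·0.02 = 4.49%.
- Month 17: 0.0256 + 0.9681·0.04 = 6.43%.
- Month 25: 8.37%, although starts have not changed since month 17.

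A segmented fit on the logit scale gives a level OR of 1.53 and a slope-change OR of 1.034 per month. Over d = 0.1–0.3 and v = 0.33 or 1.0, the level OR is 1.19–1.67 and the slope-change OR 1.029–1.053. With active users excluded, the same step gives 2.04 and 1.000.

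**4. No effect**

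If p does not change and the pool is stable, q does not change. Existing users then produce neither a false level change nor a false slope change.

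**5. AUDIT-C-only patients**

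Let s be their share of the cohort. The full-cohort rate is (1 − s)·(rate in diagnosed) + s·(rate in AUDIT-C-only). Suppose diagnosed patients go from 2% to 4% (OR 2.04) and s = 0.3. If AUDIT-C-only patients stay at 1%, the cohort goes from 1.70% to 3.10% (OR 1.85). If they rise from 1% to 4%, it goes from 1.70% to 4.00% (OR 2.41). The direction is open.

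**The case against.** The strongest reply is that the outcome sentence is shorthand. It stands under a hypothesis about directly targeted patients and ends with the targeted appointment. Elsewhere the article also says AUD diagnosis where the cohort is wider: the Abstract describes the mailing as going to veterans with AUD diagnoses, although AUDIT-C-only patients qualify too. That reading is possible, and it rules out saying that the plan has decided to count refills. But it is not stated, and the sentence spells out its own denominator, which conflicts with the cohort. This is a conflict in the text, not a detail left to an analysis plan.

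Stronger conclusions that a reader might infer are not supported:

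- **Refills dominate the outcome.** The article does not give the share with an active prescription among primary care attenders at these sites.
- **Refills create a spurious finding.** A stable pool is absorbed in the pre-intervention level. The extra slope appears only if starts have truly risen, and the effect then moves between two terms that are both tested.
- **Refills cannot reflect the intervention.** Later refills by new starters follow from treatment that it prompted.
- **The AUDIT-C omission also dilutes.** Step 5 shows that it need not.
- **A fill before the appointment could count.** The sensitivity windows are described as following the visit, and the parallel secondary hypothesis says that patients then fill. In context, the window runs forward.

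**Conclusion.** The point holds as a conflict between the primary outcome and the population of its own hypothesis. Applied as written, the outcome attenuates the odds ratio that the planned model estimates and shifts part of a step effect from level to slope; both come from the refill component alone. Under the assumed 2–5% on medication, 60–80% refilling and 0.5–1% new starts, a doubling of starts appears as an OR of about 1.11–1.46. On the absolute scale the loss is small (factor 0.95–0.98). These sizes are illustrative, because none of the three inputs is in the article. The AUDIT-C omission is a population mismatch of unknown direction. If the cohort criteria were meant to apply, the outcome definition must say so.

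**What to change.** State one cohort algorithm and apply it identically in all 16 pre-intervention and 9 intervention months and at the comparison sites: AUD diagnosis or AUDIT-C > 8 in the past 12 months, no active AUD prescription on the identification date, and a primary care appointment within 30 days. The pre-intervention months matter because the cohort is identified for intervention purposes only during the 9 months; using it after onset and the diagnosis-only definition before would change the population at month 17.

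Count as an event a first fill from the identification date to 1 month after the appointment. Starting the window at the appointment would lose starts prompted by the mailing or provider alert, both of which precede the visit. Keep the all-diagnosed, any-fill rate as a sensitivity analysis, and use the same definition in the parallel hypotheses.

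The cost is a wording change and a changed pull from administrative records. The downside is a lower absolute event rate.
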